### 14.2.3 ANALYSIS OF SECONDARY OUTCOMES

The analysis will be performed primarily in FAS, with a secondary analysis in PPS.

| Background information/primary outcome/secondary outcomes                                 | FAS/PPS                      | Statistics                                                                                                                                                                                                                                                                                                                                                                                                                                                                                                                                                                                                                                         |
|-------------------------------------------------------------------------------------------|------------------------------|----------------------------------------------------------------------------------------------------------------------------------------------------------------------------------------------------------------------------------------------------------------------------------------------------------------------------------------------------------------------------------------------------------------------------------------------------------------------------------------------------------------------------------------------------------------------------------------------------------------------------------------------------|
| Secondary outcomes                                                                        |                              | Intervention group vs. control group                                                                                                                                                                                                                                                                                                                                                                                                                                                                                                                                                                                                               |
| A. Efficacy evaluation items for mother                                                   |                              |                                                                                                                                                                                                                                                                                                                                                                                                                                                                                                                                                                                                                                                    |
| Days from the onset of pPPROM to delivery                                                 | Mainly FAS, followed by PPS. | (1) Cox proportional hazards model: hazard ratio and 95% CI. (2) Kaplan-Meier curve, (3) by stratified Cox proportional hazards model stratified by stratified factors**.                                                                                                                                                                                                                                                                                                                                                                                                                                                                          |
| Gestational weeks at delivery                                                             |                              | (1) Summary statistics**, (2) box-plots, (3) (1) and (2) according to stratified factors**.                                                                                                                                                                                                                                                                                                                                                                                                                                                                                                                                                        |
| Reasons of pregnancy termination                                                          |                              | (1) list of reasons for termination of pregnancy, (2) the numbers and frequencies of reasons for pregnancy according to therapy groups, (3) (2) according to stratified factors*.                                                                                                                                                                                                                                                                                                                                                                                                                                                                  |
| Findings at delivery (mode of delivery, presence/absence of stillbirth, placental weight) |                              | A: mode of delivery
(1) list of mode of delivery (spontaneous vaginal delivery, induced vaginal delivery, cesarean section, vacuum delivery, breech delivery), (2) the numbers and frequencies of the list according to therapy groups, (3) (2) according to stratified factors**.
B: presence/absence of stillbirth
(1) the numbers, frequencies, and 95% CI, (2) the difference in frequency and 95% CI, (3) adjusted risk difference and 95% CI by the Mantel-Haenszel method, adjusted for stratified factors**.
C: placental weight
(1) Summary statistics*, (2) Box-plots, (3) (1) and (2) adjusted for stratified factors**. |
| Incidence rate of IUFD                                                                    |                              | (1) the numbers, frequencies, and 95% CI, (2) the difference in frequency and 95% CI, (3) adjusted risk difference and 95% CI by the Mantel-Haenszel method, adjusted for stratified factors**.                                                                                                                                                                                                                                                                                                                                                                                                                                                    |
| Incidence rate of histological chorioamnionitis                                           |                              | (1) the numbers, frequencies, and 95% CI, (2) the difference in frequency and 95% CI, (3) adjusted risk difference and 95% CI by the Mantel-Haenszel method, adjusted for stratified factors**.                                                                                                                                                                                                                                                                                                                                                                                                                                                    |
| Rate of cesarean delivery                                                                 |                              | (1) the numbers, frequencies, and 95% CI, (2) the difference in frequency and 95% CI, (3) adjusted risk difference and 95% CI by the Mantel-Haenszel method, adjusted for stratified factors**.                                                                                                                                                                                                                                                                                                                                                                                                                                                    |
| Incidence rate of placental abruption                                                     |                              | (1) the numbers, frequencies, and 95% CI, (2) the difference in frequency and 95% CI, (3) adjusted risk difference and                                                                                                                                                                                                                                                                                                                                                                                                                                                                                                                             |

|                                                                                              |                              |                                                                                                                                                                                                 |
|----------------------------------------------------------------------------------------------|------------------------------|-------------------------------------------------------------------------------------------------------------------------------------------------------------------------------------------------|
|                                                                                              |                              | 95% CI by the Mantel-Haenszel method, adjusted for stratified factors**.                                                                                                                        |
| B. Efficacy evaluation items for infant                                                      |                              |                                                                                                                                                                                                 |
| Incidence rate of BPD 28                                                          | Mainly FAS, followed by PPS. | (1) the numbers, frequencies, and 95% CI, (2) the difference in frequency and 95% CI, (3) adjusted risk difference and 95% CI by the Mantel-Haenszel method, adjusted for stratified factors**. |
| Perinatal death rate (total of IUFD + early neonatal death / total of neonatal live infants) |                              | (1) the numbers, frequencies, and 95% CI, (2) the difference in frequency and 95% CI, (3) adjusted risk difference and 95% CI by the Mantel-Haenszel method, adjusted for stratified factors**. |
| Rate of infantile deaths until just before discharge of the infants                          |                              | (1) the numbers, frequencies, and 95% CI, (2) the difference in frequency and 95% CI, (3) adjusted risk difference and 95% CI by the Mantel-Haenszel method, adjusted for stratified factors**. |
| Birth weight                                                                                 |                              | (1) Summary statistics*, (2) box-plots, and (3) (1) and (2) according to stratified factors**.                                                                                                  |
| Birth height                                                                                 |                              | (1) Summary statistics*, (2) box-plots, and (3) (1) and (2) according to stratified factors**.                                                                                                  |
| Birth head circumference                                                                     |                              | (1) Summary statistics*, (2) box-plots, and (3) (1) and (2) according to stratified factors**.                                                                                                  |
| Day of hospitalization (from the birth date to discharge)                                    |                              | (1) Summary statistics*, (2) box-plots, and (3) (1) and (2) according to stratified factors**.                                                                                                  |
| Day of invasive ventilation                                                                  |                              | (1) Summary statistics*, (2) box-plots, and (3) (1) and (2) according to stratified factors**.                                                                                                  |
| Day of non-invasive ventilation                                                              |                              | (1) Summary statistics*, (2) box-plots, and (3) (1) and (2) according to stratified factors**.                                                                                                  |
| Day of oxygen administration                                                                 |                              | (1) Summary statistics*, (2) box-plots, and (3) (1) and (2) according to stratified factors**.                                                                                                  |
| Incidence rate of infants with surfactant administration                                     |                              | (1) the numbers, frequencies, and 95% CI, (2) the difference in frequency and 95% CI, (3) adjusted risk difference and 95% CI by the Mantel-Haenszel method, adjusted for stratified factors**. |
| Incidence rate of infants with RDS                                                           |                              | (1) the numbers, frequencies, and 95% CI, (2) the difference in frequency and 95% CI, (3) adjusted risk difference and 95% CI by the Mantel-Haenszel method, adjusted for stratified factors**. |
| Incidence rate of infants with PPHN                                                          |                              | (1) the numbers, frequencies, and 95% CI, (2) the difference in frequency and 95% CI, (3) adjusted risk difference and 95% CI by the Mantel-Haenszel method, adjusted for stratified factors**. |
| Incidence rate of infants with IVH                                                           |                              | (1) the numbers, frequencies, and 95% CI, (2) the difference in frequency and 95% CI, (3) adjusted risk difference and 95% CI by the Mantel-Haenszel method, adjusted for stratified factors**. |
| Incidence rate of infants with PVL                                                           |                              | (1) the numbers, frequencies, and 95% CI, (2) the difference in frequency and 95% CI, (3) adjusted risk difference and 95% CI by the Mantel-Haenszel method, adjusted for stratified factors**. |
| Incidence rate of infants with sepsis                                                        |                              | (1) the numbers, frequencies, and 95% CI, (2) the difference in frequency and 95% CI, (3) adjusted risk difference and 95% CI by the Mantel-Haenszel method, adjusted for stratified factors**. |
| Incidence rate of infants with NEC                                                           |                              | (1) the numbers, frequencies, and 95% CI, (2) the difference in frequency and 95% CI, (3) adjusted risk difference and 95% CI by the Mantel-Haenszel method, adjusted for stratified factors**. |
| Incidence rate of infants with symptomatic PDA                                               |                              | (1) the numbers, frequencies, and 95% CI, (2) the difference in frequency and 95% CI, (3) adjusted risk difference and                                                                          |

95% CI by the Mantel-Haenszel method, adjusted for stratified factors\*\*.

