|                     | 
incidence rate of BPD28, perinatal death rate (total of IUFD + early neonatal death / total of neonatal live infants), rate of infantile death until just before discharge to home of the infants, birth weight, birth height, birth head circumference, day of hospitalization (from the birth date to discharge to home), day of invasive ventilation, day of non-invasive ventilation, day of oxygen administration, incidence rate of infants with surfactant administration, incidence rate of infants with RDS, incidence rate of infants with pulmonary hypertension in the neonate, incidence rate of infants with IVH, incidence rate of infants with PVL, incidence rate of infants with sepsis, incidence rate of infants with NEC, incidence rate of infants with symptomatic patent ductus arteriosus.
 
Secondary outcomes (Safety evaluation items for mother and fetus): incidence rates of adverse events or side effects, incidence rates of serious adverse events or serious side effects, incidence rates of critical adverse events (IUFD, sepsis of mother, admission to intensive care unit of mother, multiple organ disorders of mother, artificial ventilation for mother, hysterectomy for mother).
 
Secondary outcomes (Safety evaluation items for infants): incidence rates of serious adverse events.
 
Secondary outcomes (Other evaluation items in the current trial): detection rate of Ureaplasma spp. (in vagina, on surface of the placenta, in infantile pharynx, and in infantile ear cavity).
 |

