Some infants with moderate/severe BPD36 show continued respiratory failure beyond the neonatal period, and they need long-term oxygen and/or respiratory support. After school age, central nervous system effects are also seen, including decreased brain capacity and lower IQ in cognitive and language development. Although much research and treatment has been done, the incidence is still high, around 50%, and has a significant impact on the prognosis of very low birth weight infants.

It has been reported that pPROM is an independent risk factor for BPD. We analyzed 55 pregnant women with singleton pregnancy who had pPROM at <28 weeks of gestation, and delivered between 22 and 31 weeks of gestation, and we investigated the association between pPROM and the subsequent occurrence of short- and long-term prognoses; perinatal death occurred in 13% (intrauterine death: 6%, early neonatal death: 7%), pulmonary hypoplasia in 14%, respiratory distress syndrome (RDS) in 56%, transient tachypnea of newborn (TTN) in 42%, NEC

in 6%, IVH in 10%, PVL in 10%, sepsis in 4%, BPD at 28 days of life (BPD28) in 72%, and BPD36 in 60% .

Since supportive care such as oxygen therapy is the only treatment for BPD, the prevention of BPD is strongly desired. To this end, it is very important for women with pPROM occurring at <28 weeks of gestation to receive appropriate antibiotics, and to prolong the pregnancy period.

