#### **Secondary outcomes (Efficacy evaluation items for child)**

BPD28 occurrence rate  
 Perinatal mortality (intrauterine fetal death + early neonatal death) rate  
 Percentage of deaths before discharge  
 Birth weight, birth height, birth head circumference  
 Hospitalization days (birth date to discharge date)  
 Invasive artificial ventilation days  
 Non-invasive artificial ventilation days  
 Number of days when oxygen was administered  
 Percentage of children who required surfactant administration  
 Neonatal RDS incidence rate  
 Prolonged pulmonary hypertension incidence rate  
 Intracranial hemorrhage incidence rate  
 PVL incidence rate  
 Percentage of sepsis  
 NEC incidence rate  
 Symptomatic ductus arteriosus incidence rate

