### 5.2.2 REASONS FOR SETTING THE NUMBER OF CASES

In this study, since fetal and neonatal deaths were considered to be at higher risk of developing BPD and infant deaths up to 36 weeks PMA were also considered as one of events, infant deaths up to 36 weeks PMA (5%) were also taken into account to establish effect sizes for the two groups.

In a previous foreign study, the incidence of BPD36 was 26.4% (29/110, all children survived) when 110 pregnant women who developed pPROM at <28 weeks of gestation were treated with AZM. In a previous study in Japan, the incidence of BPD36 was 18.2% (2/11, all children survived) when 11 pregnant women with pPROM at <28 weeks of gestation were treated with ABPC/SBT + AZM. In addition, when ABPC/SBT + AZM was administered to 10 pregnant women with pPROM at <28 weeks of gestation from June 2013 to May 2020 at Saga Hospital, the incidence of BPD36 was 40.0% (4/10, all children survived) ([name] *et al*, unpublished data). Based on the above, the incidence of moderate or severe BPD36 or child death by 36 weeks PMA in the intervention group (AZM group) was assumed to be 18.0% to 40.0%.

On the other hand, the literature search did not retrieve any reports of EM administration to pregnant women with pPROM at <28 weeks' gestation alone. Therefore, we assumed that the incidence rate of moderate or severe BPD36 or infant death by 36 weeks PMA in the control group (EM group) was 60.0% based on the general BPD36 incidence rate.

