#### (5) BPD28 presence/absence

The presence or absence of BPD28 onset is defined as "the presence or absence of oxygen or respiratory support use at day age 28."

Time of implementation: Day 28\*1 (±2 days)

\*1: For children discharged by day 28, evaluation is performed at the 1-month check-up.

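### The perinatal death rate counts fetal deaths in its numerator but leaves them out of its denominator, so the interval and risk differences planned for it do not fit

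*Protocol*

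**What the plan says.** The definition appears in three places in the protocol.

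- Section 14.2.3, part B (infant efficacy items): "Perinatal death rate (total of IUFD + early neonatal death / total of neonatal live infants"). The statistics ordered for this row are numbers, frequencies and 95% CI; the difference in frequency with 95% CI; and a Mantel-Haenszel adjusted risk difference over the two stratification factors. The FAS is the main set and the PPS the second.
- Section 1.1, evaluation items: "perinatal death rate (total of IUFD + early neonatal death / total of neonatal live infants"), which is the same denominator.
- Section 3, child efficacy items: "Perinatal mortality (intrauterine fetal death + early neonatal death) rate". The numerator is given and no denominator.

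Section 2.1.1 reports the same outcome in the investigators' own series of 55 women: "perinatal death occurred in 13% (intrauterine death: 6%, early neonatal death: 7"%). The two components are added, which implies a common denominator, although that denominator is not stated.

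**The concern.** A fetus that dies in utero is never a live infant. Under the stated definition it adds one to the numerator and removes one from the denominator. The quantity is therefore not the share of any defined group that died.

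All three planned statistics assume that it is. A confidence interval for a frequency treats the numerator as a count out of the denominator. The Mantel-Haenszel risk difference needs events and non-events in each arm and stratum that add up to the subjects there.

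What is at stake is a mortality outcome in a trial where IUFD is also a critical adverse event (section 9.1.2). As written, the level is overstated. Any imbalance in fetal loss between arms is exaggerated, in whichever direction it falls.

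**Working it through.** **Inputs.** From section 2.1.1: IUFD 6%, early neonatal death 7%, perinatal death 13%. From section 5.2.1: 50 per arm. The IUFD and early-death counts per arm below are assumptions for illustration. The denominator wording is read as live-born infants.

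**The protocol's own figure.** 6% + 7% = 13%. This reproduces the background rate and works only if both components share one denominator.

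**Formulas.** Let N be pregnancies (all singleton), i the IUFDs and e the early neonatal deaths.

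- On all births: (i + e) / N
- As written: (i + e) / (N − i)
- Inflation factor: N / (N − i) = 1 / (1 − IUFD rate)

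**At the background rates.** As written, 0.13 / 0.94 = 13.8%, against 13.0% on all births. That is 0.8 points more, a factor of 1/0.94 = 1.06.

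**In an arm of 50 with assumed counts (e = 4 throughout).**

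| IUFD | On all births | As written |
|---|---|---|
| 3 | 7/50 = 14.0% | 7/47 = 14.9% |
| 6 | 10/50 = 20.0% | 10/44 = 22.7% |
| 12 | 16/50 = 32.0% | 16/38 = 42.1% |
| 25 | 29/50 = 58.0% | 29/25 = 116% |

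The last row is not a realistic scenario. It shows that the quantity is not bounded by 100% and so is not a proportion.

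**Between-arm contrast.** With 3 IUFD in one arm and 6 in the other:

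- On all births: 20.0% − 14.0% = 6.0 points.
- As written: 10/44 − 7/47 = 22.7% − 14.9% = 7.8 points.

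With equal IUFD counts and equal early deaths in two arms of 50, both versions give a difference of zero.

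**Why the planned statistics fail.** Take 3 IUFD and 4 early neonatal deaths in 50 pregnancies. The infants alive after the early neonatal period number 50 − 3 − 4 = 43. A 2×2 table built from the written definition would have 47 − 7 = 40 non-events, because the three fetal deaths are subtracted twice. No set of subjects corresponds to that table.

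**The case against.** The strongest reply is that this matters little. It is one of many secondary outcomes in an exploratory phase II trial of 100. The distortion at the expected rates is under one point. IUFD has its own row in section 14.2.3 with numbers tabulated, so a reader could rebuild the correct rate. All of that stands, and it limits the weight of the point. It does not rescue the definition. The protocol states the denominator in two sections, so it is not a detail left to the SAP. A ratio to live births could be shown descriptively, but not with the statistics ordered for it.

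It is also fair that section 2.1.1 does not say its percentages are over all 55 women. The common denominator is inferred from the addition.

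A reader might go further and infer that death is mishandled across the infant outcomes. BPD28 is defined as "the presence or absence of oxygen or respiratory support use at day age 28", and rows such as "Day of oxygen administration" receive plain summaries in the FAS. An infant who dies early might then count as free of BPD28 with few support days, so that an arm with more deaths looks better. The documents do not support this as an error, for these reasons.

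- The protocol is silent on how such infants enter, and the rule may sit in the SAP, which is not shown.
- Hospital days run from birth to discharge or transfer (section 7.5.3), so for a death they are undefined rather than short.
- The duration outcomes are descriptive only.
- Death is visible in the primary composite, the IUFD rate, the perinatal death rate and death before discharge.

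Section 5.2.2 does say that "infant deaths up to 36 weeks PMA were also considered as one of events", but that concerns the primary outcome.

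The conditional effect can be sized. Assume that BPD28 is 72% among survivors; section 2.1.1 gives 72% without stating its denominator. If deaths were kept as BPD28-absent, the rate would be 0.72 × 0.95 = 68.4% at 5% mortality, 0.72 × 0.87 = 62.6% at 13% and 0.72 × 0.77 = 55.4% at an assumed 23%. If deaths were excluded, it would stay at 72% unless the infants who die differ in BPD risk.

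**Conclusion.** The point holds for the perinatal death rate. As defined in sections 1.1 and 14.2.3 it is not a proportion, and the 95% CI, difference in frequency and Mantel-Haenszel risk difference planned for it are not valid. The level is inflated by 0.8 points (13.0% to 13.8%) at the protocol's background rates. A difference in IUFD between arms is stretched, for example from 6.0 to 7.8 points under the assumed counts of 3 against 6 IUFD with 4 early neonatal deaths in each arm of 50. The invalidity follows from the definition alone; only the sizes depend on the rates and counts used.

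This is a small error on a secondary outcome. The primary analysis and the stated power (0.516 to 0.995) do not depend on it.

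The handling of infants who die in BPD28 and in the oxygen, ventilation and hospital-day summaries is a secondary note. If they are kept in the FAS as BPD28-absent or with truncated days, those outcomes can look better in an arm with more deaths. The protocol does not say that this will be done.

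**What to change.** In sections 1.1 and 14.2.3, define the perinatal death rate as IUFD plus early neonatal deaths, divided by all pregnancies in the analysis set (IUFD plus live births). Give the same denominator in section 3, where none is stated. The planned statistics can then stay as they are.

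The cost is a line of wording in each section. No new data are needed, since stillbirth and infant death are already recorded.

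As a check rather than a correction, confirm before analysis that the SAP states how infants who die enter BPD28 and the duration summaries. Several rules are reasonable: a composite of BPD28 or death, a stated survivors-only analysis, or days alive and free of support. The protocol does not need to adopt any particular one.
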